# **ETHICAL CONSIDERATIONS**

## **Considerations in connection with the study as a whole**

Ropivacaine is a known and registered medicine.

The applied block is performed under ultrasound guidance and is not deemed to be associated with complications.

Patients are prescribed supplemental analgesics corresponding to current practice, and therefore there are not deemed to be ethical problems in this study.

The study will be conducted in accordance with the principles of the Declaration of Helsinki. The protocol will be submitted to the local Research Ethics Committees, the Danish Medicines Agency and the Danish Data Protection Agency for approval. The investigator will also inform the Research Ethics Committee, the Danish Medicines Agency and the Danish Data Protection Agency of any significant or major changes in the protocol. The study will be reported in the international database clinicaltrials.gov.

All patients taking part in the study must provide their oral and written informed consent before they are included in the study. It is the investigator's duty to inform patients so that they are fully aware of all aspects of the survey.

Patients may at any time withdraw their consent to participation in the survey. If the patient decides to do this, this will not impair the patient's relationship with the investigator and the patient will continue to receive the best treatment the unit can offer.

Taking part in the trial gives patients the opportunity to administer the analgesic treatment themselves, which has been shown in a large study to give a high level of patient satisfaction. It is our expectation that the Ropivacaine group (Group A) will have more optimal pain management, with fewer opioid-related side effects. Apart from the possibility of adjusting their pain treatment themselves, patients will not benefit directly from the treatment. However, it is hoped that the information gathered will result in improved pain management after revision knee arthroplasty in the future.

**Risks, side effects, disadvantages, etc.**

We believe that this study does not involve side effects or risks that exceed those normal for this operation. The drugs used in the trial are well known and have few side effects, so it is judged that participation in the trial is associated with very low risk. In the same way, we hope to reduce the need for morphine after surgery, which could also mean fewer side effects. In addition, patients receive additional analgesic treatment according to usual practice, which is why no ethical problems are seen in this study.

The applied block is inserted under ultrasound guidance and not deemed to be associated with complications.

Participation in the trial is not expected to result in additional hospitalization time or investigations than described above.

## **Information about and consent from patients**

All patients registered for revision knee arthroplasty under general anaesthesia at the Rigshospital's Department of Orthopaedic Surgery Department U will be invited to take part in the trial. The first contact with the patient will take place upon admission the day before surgery. At this point, the written information (Annex 1) is given to the patient and the patient is informed verbally about the trial. At the beginning of the meeting, the patient will be informed that they have the possibility of having a companion present. If necessary, there will be a wait until the arrival of the companion before the information interview is held. The verbal information will be given by one of the investigators, Consultant [name], Consultant [name] or Doctor [name]. The interview will be conducted in a closed room without distractions or interruptions. The patient will be given time to consider the request.

Consent shall be obtained on the day of surgery at the latest. From the time the written and oral information is given, the patient will have around a day of reflection before consent is obtained.

After agreement, the trial subjects will receive comprehensive verbal and written information about the aims, processes, potential benefits and risks of the trial, as well as the block type and local anaesthetic employed, including any possible side effects that these might have. Subjects will be informed that they are entitled to a period of deliberation before consent is given, and that they have the right to have a companion present when the information is given. The subjects will also be informed that participation is voluntary and that they may withdraw from the trial at any time. Subjects will be informed as to what treatment they will receive if they choose not to participate or wish to withdraw from the trial.

Patients will be informed that randomization will take place on the day of surgery.

Informed written consent will be received from all subjects before inclusion in the trial.

A copy of the information and consent declaration will be given to the subjects.

Relevant provisions of the Research Ethics Committee regarding informed consent will be followed. The information and consent declaration for patients is attached (Annex 1).

## **Protection of patient data**

All information will be treated confidentially and in the reporting of study results, patients will be anonymous and the persons responsible for this trial are bound to confidentiality.

The investigator will create an identification list of all patients who have been given trial numbers. This list will contain the full name and CPR number (Annex 3).

Data collected in the form of a Case Report Form and records will only be made available to third parties in accordance with Danish law, which means in connection with monitoring by Copenhagen University Hospital's GCP unit, as well as upon inspection by authorized representatives of the relevant authorities.

Patients will be informed in writing that the results will be stored and analysed in a computer, that all information will be treated confidentially and that patients will be anonymous in the reporting of the results of the trial. They will also be informed that local data legislation will be observed.

Patients will also be informed in writing of the possibility of a review by public authorities in the event that they require access to relevant information and that Copenhagen University Hospital's GCP Unit will also have access to this information.

The investigator will allow the project to follow the rules of Good Clinical Practice.

# **FRAMEWORK FOR THE STUDY**

## **Schedule**

The study is scheduled to start: 01.08.10. The study is scheduled for completion: 01.02.14

## **Location of the study:**

Department of Anaesthesia and Department of Orthopaedic Surgery, Centre of Head and Orthopaedics, Rigshospitalet.

## **Study Design**

**Type of trial:** Placebo-controlled

**Randomization:** Computer-generated randomized lists, sealed envelopes, block randomization of 10 patients.

**Blinding:** Double-blind

**Participants:** Patients set to undergo knee arthroplasty under general anaesthesia

**Number:** 34(evaluable patients)

# **STUDY SELECTION**

## **Inclusion criteria.**

Patients must meet all the following criteria to be suitable for inclusion in the study:

- Age > 40 < 85 years old
- Patients scheduled for total knee arthroplasty in general anaesthesia with Propofol and Ultiva.
- Patients who gave their written informed consent to participating in the study after having fully understood the contents of the protocol and restrictions.
- ASA 1-3.
- BMI > 18 and < 40

## **Exclusion criteria.**

Patients who meet one or more of the following criteria are not suitable for inclusion in this study:

- Patients who cannot cooperate with the study.
- Patients who cannot understand or speak Danish.
- Patients with allergy to the medicines used in the study.
- Patients suffering from alcohol and/or drug abuse – based on the investigator's opinion.

## **Financial situation**

This study was investigator-initiated. Costs in connection with the study relate to the various notifications, and the study medication. The costs of the various notifications are met by [name] research account, and the costs of study medication are met by the Department of Anaesthsia, HOC, Rigshospitalet. There will be no external support for the study. The investigator has no financial interest in the trial.

## **Patients' completion of and withdrawal from the trial**

- A patient who has completed the study is a patient who has followed the trial's treatment plan for the prescribed initial 24 hours postoperatively.
- A patient who has not completed the study is a patient included in the trial, i.e. who has given informed consent, but does not complete the trial, whether the patient has received the trial medication or not.
- If a patient does not complete the trial an account should be given as to whether and how this subject is followed in the trial – this also applies to drop-outs – as well as what data has been collected from these subjects.

## **Reasons for patients' withdrawal from the trial**

A patient can be withdrawn from the trial under the following conditions:

- If the investigator believes that a change of treatment will be best for the patient
- If the patient wishes to withdraw from the trial
- Violation of protocol rules

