## **Endpoints**

#### Primary end points

- Pain score with 45 degree active flexion of the knee (VAS) 4 hours postoperatively.

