## **Procedure for patients who withdraw from the trial**

In accordance with the Declaration of Helsinki, patients have the right to withdraw from the trial at any time for any reason. The investigator also has the right to withdraw a patient from the trial at any time.

The reason why a patient is withdrawn from the trial before the scheduled time shall be recorded in the patient's Case Report Form.

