# **METHODOLOGY**

## **General treatment plan and medication dosage**

- An examination is made of whether the patient meets the inclusion and exclusion criteria.
- The trial period is 24 hours with T0 = last suture.
- **Standard pre-medication:**
  - 1 hour before arrival in the operating theatre: Paracetamol 1 g per os.
- **Ultrasound-guided insertion of catheter in the Adductor Canal:**
  - The catheter is inserted under ultrasound guidance under general anesthesia.
- **Treatment A**:
  - Adductor Canal Block via catheter inserted with ultrasound guide, with Ropivacaine 0.75%, bolus 30 ml 0 hours postoperatively, followed by bolus with Ropivacaine 0.75%, 15 ml 6 hours postoperatively. At 6 hours postoperatively an infusion catheter is connected with an infusion of Ropivacaine 0.2%, 9 ml per hour. The pump remains connected until the end of the trial 24 hours postoperatively.
- **Treatment B**:
  - Adductor Canal Block via catheter inserted with ultrasound guide, with placebo, isotonic NaCl, 30 ml bolus 0 hours postoperatively, followed by bolus of NaCl, 15 ml, 6 hours postoperatively. At 6 hours post-operatively an infusion catheter is connected with an infusion of isotonic NaCl, 9 ml per hour. The pump remains connected until the end of the trial 24 hours postoperatively.
- **Standard anaesthesia:**
  - General anaesthesia with Propofol and Remifentanil
  - Rocuron 0.5 mg/kg for intubation, no reversal with neostigmine
  - With a fall in blood pressure, ephedrine is given, alternatively metaoxedrin
  - Fluids as needed
  - 30 minutes before the end of anaesthesia, morphine 0.2 mg/kg is given iv
- **Standard postoperative nausea and pain treatment:**
  - Given postoperatively and for the rest of the 24-hour trials starting T0 + 2 hours:
    - Paracetamol 1 g every 6 hours po.
    - Ibuprofen 400 mg every 6 hour if there are no contraindications.
  - Patient-controlled iv morphine (PCA), bolus 2.0 mg, lockout time 15 minutes. Mixture: Morphine 1 mg/ml.
  - In the first hour postoperatively upon declaration of pronounced pain, fentanyl 0.1 mg may be given iv. The dose may be repeated after 10 minutes.
  - If there is a need for additional morphine in addition to the PCA pump, in the first 2 hours postoperatively, bolus doses of 2.5 mg morphine iv can be given on request.
  - Patients who are in regular opioid therapy preoperatively continue this treatment unchanged during the period of the trial.

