## **Clinical assessments**

- **Patient-controlled morphine consumption**:
  - Number of bolus doses delivered in the period 0-8 hours postoperatively is recorded
  - Number of bolus doses delivered in the period 0-24 hours postoperatively is recorded
- **Pain:**
  - Patients' pain is recorded on a Visual Analogue Scale (VAS) of 100 mm, where 0 = no pain and 100 = worst possible pain. Patients state their own pain intensity.
  - Pain is recorded at rest and in connection with 45 degrees active flexion of the knee.
  - Pain is recorded preoperatively before administration of medication, as well as 1, 2, 4, 6, 8 and 24 hours postoperatively, corresponding to the end of the trial period.
- **Side effects:**
  - Nausea and sedation are recorded on a verbal scale (none, mild, moderate, severe) 1, 2, 4, 6, 8 and 24 hours post-operatively.
  - The number of productive vomiting events (volume estimated over 10 ml) is recorded corresponding to the periods 0-1, 1-2, 2-4, 4-6, 6-8 and 8-24 hours post-operatively by interview with the patient.
  - The patient's use of Zofran (mg) 0-8 and 0-24 hours postoperatively is recorded.

The study extends for each patient from introductory conversation to 24 hours postoperatively. The patient receives the above treatments in accordance with a computer-generated randomized list.

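### The analysis set requires 0–8 h flexion scores although the primary endpoint is the 4 h score, and a code break excludes outright, so randomised patients can be dropped and replaced (minor)

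*Protocol*

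**What the plan says.** The only primary endpoint is "Pain score with 45 degree active flexion of the knee (VAS) 4 hours postoperatively". The schedule under Clinical assessments is wider: "Pain is recorded preoperatively before administration of medication, as well as 1, 2, 4, 6, 8 and 24 hours postoperatively".

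The Data processing section admits to the statistical analysis only patients who have flexion scores for 0 to 8 h. It does not say whether every score in that window is needed. Recruitment continues until 34 patients are evaluable, and excluded patients are described, not analysed. Evaluability is settled before unblinding.

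The section Procedures in case of emergencies has a rule of its own: a patient whose code envelope is opened is excluded, with no exception for scores already taken.

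The withdrawal sections allow removal from the trial, not only from study treatment. The listed grounds include "If the investigator believes that a change of treatment will be best for the patient" and "Violation of protocol rules". Timing is open: "The investigator also has the right to withdraw a patient from the trial at any time". Afterwards the reason goes on the case report form and, for a non-completer, "an account should be given as to whether and how this subject is followed in the trial". Nothing requires the scheduled scores to continue.

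**The concern.** The evaluability window runs 4 h past the primary time point. If the full series is required, events after the primary score was recorded decide whether that score counts. The code-break rule can likewise discard a valid primary score. Because losses are replaced until 34 are evaluable, the groups analysed need not be the groups randomised.

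The withdrawal rules add to this. A patient withdrawn before 4 h need not be scored at 4 h at all. In an analgesia trial, a change of treatment may follow pain, and if the block works, severe pain is commoner on placebo. Loss on that ground would remove high placebo scores and shrink the estimated difference. Loss for other reasons, such as toxicity in the active arm, could act the other way.

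**Working it through.** **1. The plan's own figure.** Inputs from Calculation of the number of patients: placebo mean 75, SD 20, reduction 20, type 1 risk 5% (taken as two-sided; the protocol does not say), type 2 risk 20%.

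- Normal approximation: n per arm = 2 × (1.960 + 0.842)² × (20/20)² = 15.7, so 16.
- Two-sample t-test: 16.7, so 17 per arm and 34 in total, as stated.
- Drop-out: 34 / (1 − 2/36) = 36, as stated. The plan allows for 2 of 36, or 5.6%.

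**2. How a randomised patient can be lost.**

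- *Between 4 and 8 h.* The 4 h score exists. It is lost only if Data processing means the whole series. (On that reading a missed 1 or 2 h score would have the same effect.)
- *Before 4 h.* Withdrawal from the trial means the 4 h score may never be taken. Stopping the infusion cannot be the cause here: "At 6 hours postoperatively an infusion catheter is connected with an infusion of Ropivacaine 0.2%, 9 ml per hour".
- *Code break.* Exclusion at any time, independent of the withdrawal sections. The documents give no basis for a rate, so it is not quantified.

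**3. Size of the bias from pain-driven loss.** Simulation of 20,000 trials per scenario: means 75 and 55, SD 20, 4 h score clipped to 0–100 mm, blocks of 10 (Study Design), recruitment to 34 evaluable, two-sided Mann-Whitney test at 5%.

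Assumed, not in the protocol: all loss comes from patients whose trigger score exceeds 90 mm.

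- Placebo: (90 − 75)/20 = 0.75, so 22.7% exceed 90.
- Active: (90 − 55)/20 = 1.75, so 4.0% exceed 90.
- A loss probability of 0.4 among these gives 0.4 × 22.7% = 9.1% and 0.4 × 4.0% = 1.6%. That is about 1.6 placebo and 0.3 active patients with 35.9 enrolled on average, close to the planned 2 of 36. The analysed groups average 16.3 and 17.7.

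For loss before 4 h, the trigger is an earlier score correlated with the 4 h score. For loss between 4 and 8 h, the trigger is the 4 h score itself, which is the extreme case.

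| Scenario | Difference (mm) | Power |
|---|---|---|
| No loss | 19.1 | 77.8% |
| About 2 lost before 4 h, correlation 0.3 | 18.6 | 75.5% |
| Same, correlation 0.5 | 18.3 | 74.7% |
| Same, correlation 0.7 | 18.0 | 73.7% |
| About 2 lost between 4 and 8 h | 17.4 | 73.4% |
| About 1 lost before 4 h, correlation 0.5 | 18.7 | 76.1% |
| About 1 lost between 4 and 8 h | 18.3 | 75.4% |

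The no-loss difference is 19.1 rather than 20 because of the clipping. Monte Carlo error is about 0.3 points of power. A repeat of the simulation gave 18.4 mm and 75% (before 4 h, correlation 0.5) and 17.5 mm and 74% (4 to 8 h). With both means at 75 and the same loss rule, the rejection rate was 4.7%.

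**4. What keeping the patients does.** For loss between 4 and 8 h the 4 h score was already taken, so the result returns to 19.1 mm and 78%. For patients rescued before 4 h and then scored (correlation 0.5), the result depends on how far rescue lowers the VAS (assumed):

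| Rescue effect | Difference (mm) | Power |
|---|---|---|
| 10 mm | 18.3 | 75.8% |
| 20 mm | 17.6 | 71.4% |
| 30 mm | 16.8 | 66.5% |

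Against 18.3 mm and 74.7% when these patients are dropped, power is about equal or lower.

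**The case against.** The other side has a good deal to say.

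- **Rescue does not require withdrawal.** The treatment plan provides patient-controlled morphine and early extra opioid: "In the first hour postoperatively upon declaration of pronounced pain, fentanyl 0.1 mg may be given iv", repeatable, plus morphine boluses in the first 2 h. Other treatment lets the investigator give any further drug that is needed. A reader might infer that a patient needing more analgesia must leave the trial. The text does not say so: withdrawal is optional, and its wording does not mention analgesia. This stands, and it makes pain-driven loss before 4 h probably rare.
- **The whole-series reading is not established.** Data processing can be read less strictly, and a 0–8 h requirement suits the secondary AUC endpoint. This stands too. But the rule as written governs the statistical analysis in general, not the AUC alone.
- **The code-break rule is not part of the withdrawal chain.** A reader might join the two. Exclusion there follows only from opening the envelope, so it is a separate point.
- **The calculation is close to a ceiling.** It treats all planned drop-out as pain-driven. Larger falls in power, to 58–73%, appear only if 11–31% of placebo patients are lost, far above the plan's 5.6% overall allowance, so they should not carry weight.
- **Safeguards exist.** Deciding evaluability blind prevents choosing patients by arm, and exclusions are reported. Neither prevents loss that depends on outcome.
- **A statistical analysis plan may handle missing data.** It could clarify the analysis set, but it cannot recover scores that were never taken, and the exclusion rules are already in the protocol.

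**Conclusion.** The point holds as a minor one. The main defect is the mismatch between a 0–8 h evaluability rule and a 4 h primary endpoint, conditional on the whole series being required. The outright exclusion after a code break is a second, separate defect. The withdrawal sections contribute by leaving later scores optional.

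If all of about 2 losses in 36 were pain-driven, the expected difference falls from 19.1 to about 17.4–18.4 mm and power from 78% to about 73–75%. The upper end takes a correlation of 0.5 for loss before 4 h; at 0.3 the fall is slightly smaller. The loss mechanism, the 90 mm threshold and the correlations are assumptions.

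A reader might infer a risk of a false positive result. Under this mechanism there is none to speak of: the bias is towards no effect and type 1 error stays near 5%.

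**What to change.** - **Data processing:** include every randomised patient with a recorded 4 h flexion score in the primary analysis, in the assigned arm, whether or not the 6 or 8 h score is present.
- **Procedures in case of emergencies:** do not exclude after a code break; flag scores taken after unblinding.
- **Withdrawal sections:** state that a change of treatment or a protocol violation ends study treatment at most, and that the scheduled assessments continue to 24 h unless the patient withdraws consent. The investigator keeps the right to stop study treatment at any time.
- **Reporting:** show extra drugs and their times beside the 4 h score. Other treatment already puts the drugs on the case report form; the times should be added.

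The cost is a short amendment. No extra patients or visits are needed, since patients are in hospital and the scores are already scheduled. The downside is that scores taken after extra analgesia before 4 h dilute the difference. For those patients the gain is a comparison of all randomised patients, not power. Changes made after 4 h leave the primary score untouched and affect only the later scores and the 1–8 h AUC.

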## **Procedure for patients who withdraw from the trial**

In accordance with the Declaration of Helsinki, patients have the right to withdraw from the trial at any time for any reason. The investigator also has the right to withdraw a patient from the trial at any time.

The reason why a patient is withdrawn from the trial before the scheduled time shall be recorded in the patient's Case Report Form.

# **METHODOLOGY**

## **General treatment plan and medication dosage**

- An examination is made of whether the patient meets the inclusion and exclusion criteria.
- The trial period is 24 hours with T0 = last suture.
- **Standard pre-medication:**
  - 1 hour before arrival in the operating theatre: Paracetamol 1 g per os.
- **Ultrasound-guided insertion of catheter in the Adductor Canal:**
  - The catheter is inserted under ultrasound guidance under general anesthesia.
- **Treatment A**:
  - Adductor Canal Block via catheter inserted with ultrasound guide, with Ropivacaine 0.75%, bolus 30 ml 0 hours postoperatively, followed by bolus with Ropivacaine 0.75%, 15 ml 6 hours postoperatively. At 6 hours postoperatively an infusion catheter is connected with an infusion of Ropivacaine 0.2%, 9 ml per hour. The pump remains connected until the end of the trial 24 hours postoperatively.
- **Treatment B**:
  - Adductor Canal Block via catheter inserted with ultrasound guide, with placebo, isotonic NaCl, 30 ml bolus 0 hours postoperatively, followed by bolus of NaCl, 15 ml, 6 hours postoperatively. At 6 hours post-operatively an infusion catheter is connected with an infusion of isotonic NaCl, 9 ml per hour. The pump remains connected until the end of the trial 24 hours postoperatively.
- **Standard anaesthesia:**
  - General anaesthesia with Propofol and Remifentanil
  - Rocuron 0.5 mg/kg for intubation, no reversal with neostigmine
  - With a fall in blood pressure, ephedrine is given, alternatively metaoxedrin
  - Fluids as needed
  - 30 minutes before the end of anaesthesia, morphine 0.2 mg/kg is given iv
- **Standard postoperative nausea and pain treatment:**
  - Given postoperatively and for the rest of the 24-hour trials starting T0 + 2 hours:
    - Paracetamol 1 g every 6 hours po.
    - Ibuprofen 400 mg every 6 hour if there are no contraindications.
  - Patient-controlled iv morphine (PCA), bolus 2.0 mg, lockout time 15 minutes. Mixture: Morphine 1 mg/ml.
  - In the first hour postoperatively upon declaration of pronounced pain, fentanyl 0.1 mg may be given iv. The dose may be repeated after 10 minutes.
  - If there is a need for additional morphine in addition to the PCA pump, in the first 2 hours postoperatively, bolus doses of 2.5 mg morphine iv can be given on request.
  - Patients who are in regular opioid therapy preoperatively continue this treatment unchanged during the period of the trial.
  - Zofran 4 mg iv at the first indication of moderate-pronounced nausea may then be supplemented with 1 mg iv.

